### 2.3. Baseline Assessments

After obtaining the informed consent from the participants, the baseline evaluations (T0) will be performed and the following data will be collected: sociodemographic characteristics, medical and pharmacological history, vaccination records, and Multidimensional Prognostic Index (MPI) [30], evaluated considering Activities of Daily Living (ADL), Instrumental Activities of Daily Living (IADL), Short Portable Mental Status Questionnaire (SPMSQ), Mini Nutritional Assessment-Short Form (MNA-SF), Exton-Smith Scale (ESS), Cumulative Illness Rating Scale (CIRS), and the number of drugs. Specifically, comorbidities and their severity will be assessed using the CIRS, and a complete list of current medications (including dosage and therapeutic indications) will be recorded for each participant. Baseline assessments will also include evaluations of nutritional, physical, and cognitive function, as well as selected biomarkers. Data collection will be performed by trained personnel, according to a predefined operating procedure; for each domain, validated instruments will be used to ensure reliability and comparability measurements.

#### 2.3.1. Dietary Assessment

Diet will be monitored over a two-week period, taking into account the menus offered by the LTCFs and assessing the type and amount of food actually consumed (food frequency questionnaire) by the study participants [31]. Staff will be trained in interview techniques and administering the food frequency questionnaire to ensure consistency.

#### 2.3.2. Body Composition and Physical Evaluation

A comprehensive whole-body bioelectrical impedance analysis (BIA) using a tetrapolar configuration will be performed by trained personnel, according to standardized procedures. The equipment will undergo daily calibration each morning, and participants will rest in a supine position for at least 5 to 10 min before the measurement begins. Appendicular skeletal muscle mass (ASMM) will be calculated using the equations developed by Sergi et al. [32]. The appendicular skeletal muscle mass index (ASMMI) will be obtained by dividing ASMM by the subject’s height in meters squared. Anthropometric parameters (i.e., body weight, height, calf and arm circumferences) will also be collected. Additional anthropometric data—including body weight, stature, and the circumferences of the calf and upper arm—will be collected. Body weight will be measured with a precision of 0.1 kg using a standard scale, with participants wearing light clothing and no footwear. If individuals are unable to stand, a hoist scale will be employed. For those who cannot maintain an upright posture, height will be estimated based on knee-to-heel length using Chumlea’s equations [33]. Body mass index (BMI) will then be derived as weight (kg) divided by height in meters squared. Calf circumference will be recorded at the widest part of the dominant leg, while the subject is either lying down or seated with the knee bent at a 90-degree angle, using a flexible measuring tape. Mid-upper arm circumference (MUAC) will be measured at the midpoint between the acromion and the olecranon on the dominant arm. To fully assess sarcopenia, both upper limb strength and physical performance will be evaluated. Handgrip strength will be tested using JAMAR TM Plus+ electronic dynamometers (Patterson Medical, Green Bay, WI, USA) by qualified medical personnel. Each hand will be tested three times, and the final grip strength will be calculated as the average of the best results from both the dominant and non-dominant hands.

Physical performance will be evaluated by the 6-min walking test and Short Physical Performance Battery (SPPB), which includes standing balance tests (side-by-side stands, semi-tandem test, and tandem test), gait speed measurement, and timed chair stands test, generating scores between 0 and 12, with higher scores indicating better physical performance [34].

#### 2.3.3. Neuropsychological and Psychological Assessments

Standardized neuropsychological batteries and tests will be administered to all participants before starting the training to assess their cognitive functioning; assessments will be carried out by trained staff. Global cognitive functioning will be measured through the Mini Mental State Examination (MMSE) [35]. Addenbrooke’s Cognitive Examination Revised (ACE-R) battery [36] will also be administered to assess cognitive functioning in different domains (e.g., global flexibility, attention/orientation, memory, fluency, language and visuospatial abilities). In addition, the WHOQOL-BRIEF will be administered to assess four domains assumed to represent the quality of life construct: physical domain, psychological domain, social relationships domain, and environmental domain [37]. The Cognitive Reserve Index questionnaire (CRIq) will be administered to quantify the cognitive reserve accumulated by individuals throughout their lives [38]. Finally, the Geriatric Depression Scale-GDS [39], Depression Anxiety Stress Scales-DASS-21 [40], and the Perceived Stress Scale-PSS [41] will also be administered. Sleep quality will be evaluated with the Pittsburgh Sleep Quality Index (PSQI, [42]).

#### 2.3.4. Biomarkers

A blood sample will be obtained from the study participants for the assessment of blood counts, lipid, glucose and metabolic profiles, vitamin D, inflammatory parameters, and a urine sample. A stool sample for gut microbiota analysis will be collected within three days from enrollment, following a predefined procedure to ensure uniform sample integrity through controlled timing, storage, and handling to preserve microbiota integrity. Metagenomic analysis will be performed to generate microbiome profiling data together with metadata associated with the investigated samples.

### 2.4. Multidomain Intervention

The multidomain intervention will involve different experts, such as geriatricians, neuropsychologists, physiotherapists, exercise science experts, clinical nutrition experts, and digital coaches. Participants will be informed of their group allocation after baseline data collection.

Data will be collected through a computer interface specifically designed for the study (REDCap) (https://project-redcap.org/ (accessed on 16 April 2025)) [43,44].

#### 2.4.1. Nutritional Intervention

The nutritional history of the participants will be evaluated at the beginning and at the end of the intervention, and then during follow-up, by collecting food habit data with a food frequency questionnaire.

Participants in the intervention group will be encouraged to follow a Mediterranean diet, in particular to consistently use extra virgin olive oil as the main fat source and to have a regular intake of nuts, and they will also consume functional foods, in particular sourdough-containing bread fortified with a vegetable matrix rich in polyphenols (e.g., olive leaves) and one probiotic vegetable (e.g., artichokes). Before starting the treatments, the functional foods will be evaluated for their functional properties (bioactive compounds, probiotics) [45]. Sourdough biotechnology has been demonstrated to improve digestibility and promote healthy microbiota metabolism at the colon level [46,47]. Moreover, olive leaves are considered a cheap source of polyphenols such as secoiridoids, flavonoids, phenylpropanoids, caffeic acid, tyrosol, and hydroxytyrosol [48]. The other approach will consider the use of a vegetable matrix enriched with Lacticaseibacillus paracasei IMPC2.1 probiotic strain, produced according to the innovative and patented procedures reported by Lavermicocca et al. [49,50], and authorized by the Italian Ministry of Health. Human feeding studies demonstrated that this probiotic strain is able to reach the gut in adequate amounts when delivered through vegetable matrices such as artichokes and table olives [51,52,53]. The final products will be characterized for their polyphenol content, and in vitro gastrointestinal digestion, using static and/or dynamic systems, will be employed to assess their potential health benefits. All the activities will be carried out with the companies in charge of developing the functional foods envisioned in this proposal.

#### 2.4.2. Physical Intervention

After individual evaluation, a physiotherapist or an exercise science expert will prescribe appropriate exercises for ad hoc supervised small group sessions. Each rehabilitation session will last approximately 40 min and will include a warm-up with stretching exercises (~5 min), a cool-down (~5 min), and rest periods as needed, three times a week. Exercise intensity and complexity will be tailored to each participant’s functional capacity, assessed at baseline, and progressively adapted based on performance. Based on the international guidelines for physical exercise in the old population, and considering the VIVIFRAIL Multicomponent Physical Exercise Program to Prevent Frailty and the Risk of Falls (available from https://blogs.bmj.com/bjsm/2021/03/06/vivifrail-a-multi-component-physical-training-program-to-prevent-weakness-and-falls-in-people-over-70-years/ (accessed on 16 April 2025)), participants will be asked to perform the following:Endurance exercises with muscle strengthening of the lower and upper limbs, such as getting up from a chair or bed, front and side step-ups, lifting the lower limbs, lifting water bottles, etc. The physiotherapists or exercise science experts will adapt the type of exercises to the participant’s abilities;Static and dynamic balance exercises of increasing difficulty, tailored to the patient’s initial performance level and subsequent improvements (e.g., exercises to maintain a standing position on a flat surface, load transfer, proprioceptive exercises on an unstable surface or balance board, maintaining balance on monopodal support, semi-tandem walking on a straight line, walking with small objects, etc.). If necessary, the physiotherapist or the exercise science expert will use tools to reduce the risk of falling during treatment;Exercises for aerobic activity will include walking for a number of minutes appropriate to the patient’s baseline functional performance level, following the patient’s subsequent progress during the sessions.

Exercises will be performed in small groups (3–5 participants) under continuous supervision. The VIVIFRAIL protocol, which allows for safe progression according to individual performance, will be applied, with a gradual increase in difficulty, adapted to the participant’s progress and under close observation. Each training session will include rest periods and monitoring of fatigue, pain, or changes in health status before and during sessions. Several of the following strategies will be implemented to prevent falls during exercise: At the baseline assessment, physical function and balance will be evaluated by a physiotherapist or exercise specialist prior to starting the program, to tailor exercises to each participant’s capacity, and sessions will be led by trained professionals (physiotherapists or exercise scientists) in small groups. Furthermore, participants will be monitored before and during each session for signs of fatigue, instability, or clinical changes, and sessions will be suspended or modified if safety concerns arise.

Accelerometers and other wearable sensors (smartwatches) will be used to monitor the physical activity performed. Minimally invasive wearable sensors will be used to monitor the performed activities through (a) inertial-based technologies for gait/posture analysis and (b) surface EMG-based devices for muscle activity profiling (imbalance evaluation).

Health problems and symptoms will be evaluated by the physiotherapist or the exercise science expert before starting each session. If a participant reports a significant change in health before or during the exercise, the geriatrician will be consulted. Vital signs (heart rate, blood pressure, and oxygen saturation) will be recorded at the beginning and the end of each session. Physical exercise training sessions will be stopped in the presence of (a) resting systolic blood pressure >200 mmHg or diastolic blood pressure >100 mmHg; (b) resting heart rate >120 beats/min or <40 beats/min; (c) increased heart rate 90% of maximum age during exercise; (d) oxygen saturation <90% in ambient air; (e) unusual or severe dyspnea; (f) oppressive pain or discomfort in the chest, pain in the left arm, indigestion or discomfort in the stomach; (g) palpitations; (h) severe dizziness, fainting or fainting sensation; (i) decrease in diastolic blood pressure by 20 mmHg during exercise; (j) increase in systolic blood pressure to 250 mmHg or diastolic blood pressure to 115 mmHg during exercise; or (k) decrease in oxygen saturation <88% in ambient air during exercise. The clinical conditions of the participants and the levels of intensity and duration of the exercise will be re-evaluated.

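### Four of the 11 exercise stopping criteria have no stated in-exercise measurement, one of them is not a usable heart-rate limit, and one oxygen limit does not say when it applies

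*Protocol article*

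**What the plan says.** Section 2.4.2 of the protocol article gives one schedule for the three vital signs: "Vital signs (heart rate, blood pressure, and oxygen saturation) will be recorded at the beginning and the end of each session".

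The same paragraph then gives the conditions for stopping a session, lettered (a) to (k) and joined by 'or'. Some are tied to rest, such as (a): "resting systolic blood pressure >200 mmHg or diastolic blood pressure >100 mmHg". Others are tied to exertion, such as (c), "increased heart rate 90% of maximum age during exercise", and (j), "j) increase in systolic blood pressure to 250 mmHg or diastolic blood pressure to 115 mmHg during exercise". Criterion (i), a fall in diastolic pressure of 20 mmHg, is also worded as an exercise criterion.

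There are two saturation criteria. One carries no condition of rest or exercise: "d) oxygen saturation <90% in ambient air". The other does: "k) decrease in oxygen saturation <88% in ambient air during exercise".

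Earlier in the section the article describes supervised small groups, observation before and during sessions for fatigue, pain, instability and changes in health, and suspension or modification of a session on safety grounds. Wearable devices are described for physical activity, gait and posture, and muscle activity. Section 2.4.3 adds monitoring for risk of falls.

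**The concern.** A numeric stopping criterion can act only if someone takes the reading it refers to. Four of the printed criteria refer to readings during exercise, while the printed schedule places readings at the two ends of the session. The limits in (i) and (j) are defined by a number and not by a symptom, so watching the resident cannot be relied on to detect them. The participants are aged 70 or over and exercise three times a week for six months, so these criteria are part of their protection.

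The wording of (c) and (d) raises a related problem. Staff reading (c) would have to supply the definition themselves. Staff reading (d) would have to decide whether it governs a resident who is exercising.

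**Working it through.** The plan gives no figure to reproduce here. The check is to sort each criterion by the reading it needs and compare that with the measurement the article states.

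| Criterion | What it needs | Is that measurement or observation stated? |
|---|---|---|
| (a) blood pressure, (b) heart rate | Resting value | Yes, from the reading at session start |
| (d) saturation below 90% | Saturation, condition not stated | Yes, at least at session start and end |
| (e) to (h) dyspnea, chest or stomach discomfort, palpitations, dizziness or fainting | Symptoms | Yes, through the supervision described |
| (c) heart rate | Value during exercise | No |
| (i) diastolic fall | Value during exercise | No |
| (j) systolic or diastolic rise | Value during exercise | No |
| (k) saturation below 88% | Value during exercise | No |

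**Count.** Usable as printed: 2 + 1 + 4 = 7 of 11. Without a stated in-exercise measurement: 11 − 7 = 4. For blood pressure and saturation alone the count is 3 of 11: (i), (j) and (k).

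**Does another part of the article fill the gap?** The in-session monitoring concerns symptoms, stability and clinical change. The wearables concern activity, gait, posture, muscle activity and fall risk. A smartwatch might record heart rate, but the article does not assign it that task, and it states no blood pressure or saturation function for any device. The end-of-session reading does not clearly stand in for an exercise reading, because the session includes a cool-down of about 5 minutes.

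**Criterion (c).** As worded it takes 90% of an age. An age is in years and a heart rate is in beats per minute, so the phrase yields no limit. One may guess at what was meant, but the article gives neither the quantity nor a way to compute it.

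**Criteria (d) and (k).** There are two possible readings:

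- If (d) applies at rest only, it and (k) cover different states. An exercise saturation from 88% to below 90% meets neither criterion, and the session continues as far as these two are concerned.
- If (d) applies at any time, every value below 88% is also below 90%, so (k) adds nothing. An exercise saturation from 88% to below 90% then stops the session under (d).

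The two readings lead to different actions only in that band. The text does not say which is meant.

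**The case against.** The strongest reply is that the article fixes two recording points and does not exclude readings in between. Criteria worded for exercise presuppose that someone checks during exercise, groups are small and supervised, and a journal article may leave devices and timing to the full protocol or session procedures. Part of this stands: a reader might infer that vital signs are taken only at the start and end, but the text does not say 'only'. It does not remove the point. The article prints the limits, the recording times and the stop rule together, and these do not fit one another. The point concerns what is printed, not a detail left to another document.

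Three stronger readings are tempting and are not supported:

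- **That the stopping rule as a whole cannot operate.** Seven of the 11 criteria can.
- **That (d) and (k) contradict each other.** The list pairs resting with exercise limits elsewhere: diastolic above 100 mmHg in (a) against 115 mmHg in (j), and resting heart rate in (b) against exercise heart rate in (c). This makes a resting meaning for (d) plausible. Even if (d) applies at any time, the criteria are joined by 'or', so (k) is redundant and not opposed. What is shown is a missing qualifier.
- **That the two facilities would apply different limits and produce adherence data that cannot be compared.** One text governs both, and nothing in the article shows divergent use.

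A reader might also count every session as affected: 3 × 26 = 78 per resident if six months is taken as 26 weeks, or 3 × 24 = 72 on the 24 weeks implied by 48 cognitive sessions at two per week (48 / 2 = 24). Those figures count scheduled sessions. The article gives no frequency with which any limit would be reached, so they do not measure the size of the problem.

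**Conclusion.** The point holds in a limited form. Four of the 11 stopping criteria, (c), (i), (j) and (k), rely on exercise readings for which no measurement is stated. One of those four, (c), is also not a heart-rate limit as worded. Separately, (d) lacks a condition, which leaves the action undetermined for exercise saturations from 88% to below 90%.

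This rests on the article's text alone. If the full protocol or session procedures specify in-exercise readings, the measurement gap closes in practice and the article's wording still needs aligning; the faults in (c) and (d) would need the same check. The consequence is for participant safety during sessions. The sample size, the health outcomes and the statistical analysis are not touched.

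**What to change.** The clinicians responsible for the exercise component should reconcile the paragraph in three places:

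1. Make the stated measurement times for heart rate, blood pressure and saturation match the criteria that depend on them.
2. Reword (c) so that it is a heart-rate limit that staff can compute.
3. State the condition under which (d) applies, so that its relation to (k) is clear.

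Which limits and measurement times are appropriate is for those clinicians to decide; this review does not say which is right. The cost is an editorial amendment and a line on the session form.

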#### 2.4.3. Cognitive Intervention

In the week prior to the start of the intervention, the neuropsychology team will organize face-to-face meetings to introduce the cognitive training program to the participants and to promote adherence. During these meetings, participants will also become familiar with the online platform used for the training. A cognitive intervention based on the cognitive stimulation approach will be delivered by expert neuropsychologists twice a week (48 sessions in total, approximately 30 min each). Residents will be divided into small groups (3–5 people) with similar cognitive levels, and a computerized tool will be used for the intervention (REmote stimulation for COgnitive DEcline (RECODE)). RECODE was developed by researchers at the University of Padova (https://osf.io/eqgyn/?view_only=fa14090e85f7424abf73bf583871b529 (accessed on 16 April 2025)) with the aim of stimulating multiple cognitive domains (i.e., attention, working memory, visual memory, language, orientation, and executive functions) through exercises of increasing difficulty. Each participant will use a personal laptop during the RECODE session, starting at the basic level and progressing to the next level only when they have achieved 80% accuracy in a given domain, ensuring a personalized intervention. RECODE is designed for cognitive enhancement in older people with mild-to-moderate cognitive impairment and has an age-friendly graphical interface with an avatar that interacts with the participant. Sessions will follow a fixed structure, as follows: (1) a short introduction and guidance by the neuropsychologist; (2) execution of exercises from different domains; and (3) immediate feedback from the platform and the neuropsychologist. Adherence will be monitored, and motivational strategies (group discussions, reinforcement, support from caregivers or LTCF’s staff) will be implemented to sustain participation.

Physical and cognitive interventions will be administered in a smart environment, with technological solutions including mobile and wearable devices, ensuring high acceptability by the users. In particular, smartwatches and tablets with SIM cards and pre-loaded specific applications will be used for physical and cognitive training and for monitoring specific conditions (risk of falls). Health professionals responsible for the different interventions will explain to study participants and to their family members the use of the devices (basic functions, such as turning the device on and off, and opening specific applications).

#### 2.4.4. Vaccinations

Participants in the intervention group will be encouraged to receive appropriate vaccinations according to the national vaccine calendar; for adults over 65 years of age, the national vaccine program recommends the influenza, pneumococcal, herpes zoster, and diphtheria–tetanus–pertussis vaccinations (Ministero della Salute Italiano. Italian immunisation schedule, https://www.epicentro.iss.it/vaccini/piano-nazionale-vaccini-2023–2025 (accessed on 27 June 2025)). Vaccine doses will be provided by the Department of Preventive Medicine, Vaccine Office, National Health Service, on prescription from the general practitioners.

